#### Primary outcome

* To show that TTNS therapy is superior to sham therapy in terms of average voided volume (AVV).
The endpoint is the median change in baseline at 12 weeks in AVV, registered on the daytime bladder diary. The AVV is calculated by the sum of all voids during daytime (in ml) of 3 days in total divided by the frequency of voids during daytime over 3 days in total. We consider AVV as the most relevant variable to measure efficacy since it directly reflects the functional bladder capacity. Increasing the functional bladder capacity is the key of in OAB and/or nocturnal enuresis (in the absence of nocturnal polyuria) treatment. An increased bladder capacity should ultimately lead to a decrease in micturition frequency and in urinary incontinence episodes. The follow-up interval of 12 weeks was chosen since the effect of treatment can be expected after 12 weeks of treatment.

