## Methods: participants, interventions, and outcomes

### Study setting {9}

The recruitment of participants is carried out by pediatric urologists and pediatric nephrologists from the Department of Urology and at the Department of Pediatrics at the academic hospital of the Ghent University (East-Flanders, Belgium). Children attending a pediatric specialist (PS) for urgency incontinence or bedwetting are eligible for inclusion. The inclusion criteria are listed below.

At the initial visit, the child with lower urinary tract symptoms (LUTS) is subjected to a complete diagnostic work-up according to the standard of care [9]. Besides a baseline history-taking assessment, a few additional evaluations are performed: urine sample analysis, a bladder and kidneys ultrasound (US), and an uroflowmetry with an US guided post-void residual (PVR) measurement. A 3 days daytime bladder diary and a 7 nights night-time bladder diary are distributed [10]. Based on the completed bladder diaries and the baseline work-up, children are diagnosed at the second visit and subsequently screened for eligibility.

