#### Urotherapy

Besides neuromodulation, every participant in the trial will receive the same standard Urotherapy. Urotherapy can be defined as a bladder re-education or rehabilitation program aiming for the correction of filling and voiding difficulties [13]. It encompasses the following components [10]:
Education on normal lower urinary tract (LUT) functioning and on how the LUT function of the child differs from normal.Lifestyle advices: counseling on drinking (1,5 L–2 L fluid intake daily) and voiding habits, diet, reduction of caffeine intake, proper stool management, etc.Behavioral modifications: sustaining regular voiding habits and adequate toilet positioning, avoiding holding maneuvers, etc.Regular follow-up and encouragement strategies: specifically for this trial, a follow-up visit at the physiotherapist will occur after 6 (the second visit) and 12 weeks (the third visit) of AT.Registration of symptoms, drinking, voiding, and stool habits through diaries.

Specifically for this trial, a 1-day bladder diary must be completed consistently every week as part of the urotherapy. Additionally, 3 times weekly, the participant must try to hold up urine for 5 min if the urge to urinate comes up. Gradually, the duration of delayed urinating should be trained to be increased. The so-called supervoids are part of urotherapy.

In the sixth week, a 7 day night-time bladder diary must be completed. After the second visit at the physiotherapist, the participant must continue the stimulation and urotherapy (plus completion of the diaries and supervoids) for another 6 weeks.

After the third visit, an observation period of 6 weeks is carried out during which no stimulation is given. Urotherapy however should be continued.

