#### Secondary outcomes

##### The mean volume of supervoids

This is the median change in the mean volume of three “supervoids” between week 12 and week 1, registered on the 3 days daytime bladder diary. See the “Interventions” section for the definition of supervoids. Same as for the primary outcome, this outcome reflects the change in bladder capacity.

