## Data collection and management

### Plans for assessment and collection of outcomes {18a}

Bladder diaries and the parents reported satisfaction of urinary symptoms questionnaire are distributed at the beginning of treatment on paper. The demographic data from each participant will be derived from the electronic medical record (EMR). All outcome data will be collected at the end of the 12 weeks treatment period and converted by the research assistant into a digital file. A standard frequency-volume chart with additional information of urinary incontinence episodes and urgency episodes will be used as bladder diary [10]. The parents’ reported satisfaction of urinary symptoms score is a non-validated 7 points Likert scale.

The following case report forms will be collected (see also Fig. 3 and Table 1):
-t1: First visit with the PS.

CRF with baseline patient characteristics: age, gender, presence of daytime urinary incontinence and/or enuresis nocturna, and comorbidities.

CRF with technical investigations: presence of urinary tract infection (yes/no), kidney ultrasound (US) (normal or abnormal), PVR on bladder US (ml), cystometric bladder capacity at uroflowmetry, and staccato pattern on uroflow suggestive for dysfunctional voiding (Y/N).

0: Second visit with the PS.

CRF with baseline daytime and nighttime diary parameters (volume intake, daytime diuresis, micturition frequency, AVV during the day, urgency episode (Y/N), number of urinary incontinence episodes, N of defecations, N of wet nights, nocturnal urine production, netto urine loss/night, presence of nocturnal polyuria), and parents’ reported satisfaction of urinary symptoms.

t1: First visit with the PT.

CRF with patient number, allocation group.

t2: Second visit with the PT, 6 weeks after ambulant treatment.

CRF with daytime and nighttime diary parameters after 6 weeks of treatment (same parameters as at visit 2 + averaged volume of 3 supervoids at 6 weeks) and parents reported satisfaction of urinary symptoms.

CRF with recorded (serious) adverse effects: the adverse event form.

*t3: Third and last visit with the PT, 12 weeks after ambulant therapy.

Same CRF’s as in t2.

CRF with treatment response (non-responder, partial responder, complete responder).

*t4: Third visit with the PT.

Same CRF’s as in t2.

CRF with the maintenance of treatment effect in partial and complete responders (in weeks).

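### The 12-week AVV includes the trial's deliberately delayed supervoids and the baseline AVV does not, which can raise within-arm change and response classes in both arms; the supervoid outcome itself has no pre-treatment reference

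*Protocol article*

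**What the plan says.** All references are to the protocol article.

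- **Primary outcome:** "The AVV is calculated by the sum of all voids during daytime (in ml) of 3 days in total", divided by the number of daytime voids over those days. The Abbreviations entry for AVV gives the same definition. Neither leaves any void out.
- **Urotherapy:** every participant receives it. As part of it, "3 times weekly, the participant must try to hold up urine for 5 min if the urge to urinate comes up", and "Gradually, the duration of delayed urinating should be trained to be increased". These are the supervoids.
- **The mean volume of supervoids:** this secondary outcome is the change in the mean of three supervoids "between week 12 and week 1, registered on the 3 days daytime bladder diary".
- **Study setting {9}:** "Based on the completed bladder diaries and the baseline work-up, children are diagnosed at the second visit". The baseline diary is therefore finished before enrolment. Under Study schedule, urotherapy and the first stimulation session are given later, at the first physiotherapist visit.
- **Plans for assessment and collection of outcomes {18a}:** the baseline case report form has no supervoid item. The form at the first physiotherapist visit holds only the patient number and group. The 6-week form has the "same parameters as at visit 2 + averaged volume of 3 supervoids at 6 weeks", and the 12-week visit uses the same forms.
- **Outcomes {12}:** all outcomes are to be compared with baseline measures.
- **Use of AVV change:** response is none below 50%, partial at 50-99% and complete at 100% (Study schedule). Duration of effect counts weeks of persisting response. Within-arm change is tested with the Wilcoxon signed rank test and the arms are compared with the Mann-Whitney U test (Statistical methods {20a}).

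**The concern.** AVV was chosen because it is taken to reflect functional bladder capacity. A child told to hold on before voiding produces a larger void on that occasion even if habitual voiding has not changed. If such voids enter the 12-week average but not the baseline average, part of the change comes from the instruction.

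Three results carry this directly: the within-arm tests, the response classes, and the duration of effect, which depends on those classes and is observed while urotherapy continues. A report that a given share of children responded, or that sham plus urotherapy raised AVV significantly, would mix this component with real improvement.

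The supervoid outcome has a related fault. Its reference, week 1, lies after randomisation and after stimulation has begun, so any effect within that week is subtracted out. The listed forms do not show a week-1 supervoid value being collected.

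**Working it through.** **Plan's own figure.** The document gives no supervoid volume and no void count, so there is no stated size to reproduce. From Sample size {14} the check uses only the 20-point difference, the SD of 20 and the 12 children per arm.

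**Step 1: mechanical rise in AVV.** Let F be daytime voids per day, k the supervoids on the three diary days, and r the supervoid volume relative to a usual void. With the void count held fixed, rise = k(r − 1)/(3F). Assumed: F = 6 (18 voids) and k = 3.

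- r = 1.25: 3 × 0.25/18 = 4.2%
- r = 1.5: 3 × 0.5/18 = 8.3%
- r = 2: 3 × 1/18 = 16.7%

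Over the same r, F = 5 gives 5-20% and F = 8 gives 3.1-12.5%.

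If total urine output is held fixed instead, the AVV ratio is 3F/(3F − kr + k). With F = 7 and k = 3 the rise is 3.7%, 7.7% and 16.7%. With only one supervoid on the diary days it is 1.2% to 5.0%. The largest case with r up to 2 is F = 5, k = 3: 15/12, or 25%.

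**Step 2: low end.** The only delay stated is 5 minutes, to be lengthened. Assume the full recommended intake of 1.5-2 L is voided over 14 waking hours (840 minutes), which is 1.8-2.4 ml/min. Five minutes then adds about 9-12 ml. On an assumed usual void of 120 ml, r = 1.07-1.10, and 3(r − 1)/18 is about 1-2%. On the same assumptions r = 1.25 needs about 13-17 minutes of delay and r = 2 about 50-67 minutes. The delay reached by week 12 is not stated.

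**Step 3: response classes.** Assume a normally distributed percentage change with SD 20. The share at or above 50% is 1 − Φ((50 − mean − shift)/20).

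| Assumed mean change | No shift | 8 points | 17 points |
|---|---|---|---|
| 20% | 6.7% | 13.6% | 25.8% |
| 30% | 15.9% | 27.4% | 44.0% |
| 40% | 30.9% | 46.0% | 63.7% |

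**Step 4: tests.** Simulation with 12 per arm, SD 20, 4,000 runs, and the same proportional shift for every child.

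| Quantity | No shift | 8% | 17% |
|---|---|---|---|
| Within-arm Wilcoxon rejection, no true change | 4.1% | 19.1% | 57.1% |
| Mann-Whitney type I error | 4.6% | 4.8% | 4.4% |
| Mann-Whitney power, true difference 20 | 59.9% | 61.0% | 60.9% |

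The within-arm test responds strongly to the shift and the between-arm test does not. Power near 60% rather than the stated 80% is a separate matter: 2 × (1.96 + 0.84)² × (20/20)² = 15.7, so the stated two-sided inputs need 16 per arm, not 12.

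**Step 5: the supervoid reference.** Set side by side, Outcomes {12} requires comparison with baseline, the supervoid section takes week 1, and the listed forms first record supervoids at 6 weeks. These three statements do not agree.

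**The case against.** The strongest reply is that the trial's question is TTNS versus sham and both arms receive the same urotherapy. That stands. A reader might infer that the primary comparison is biased, but a common shift leaves its type I error and power unchanged (step 4). The unblinded physiotherapist also gives the urotherapy, so supervoid coaching could in principle differ by arm; nothing in the document shows that it does. Uneven supervoid compliance could add noise, but its size has not been calculated.

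Three further limits stand:

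- Eligibility {10} admits children already treated with urotherapy, and supervoids are described as part of urotherapy. Some baseline diaries may therefore contain delayed voids. Only the trial's own supervoids are certainly absent.
- A reader might infer that the extra volume involves no bladder effect at all. The document does not support that: it treats supervoid volume as a sign of capacity, and a child who learns to hold more may have gained capacity. The arithmetic describes only the mechanical part.
- The multiples of 1.25 to 2 are assumptions. A 5-minute delay implies much less.

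On the week-1 reference, it can be said that trial supervoids do not exist before the first physiotherapist visit, so week 1 is the earliest value possible, and that the protocol expects the effect after 12 weeks, so the loss is probably small. Both are fair. They explain the choice, but the conflict with the general baseline rule and the missing week-1 item remain. A shortened form list may account for the latter, which is why it calls for reconciliation.

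**Conclusion.** The concern holds for within-arm and responder results. Followed as written, the plan averages the trial's own supervoids into the 12-week AVV and cannot do so at baseline. That can raise AVV change, response classes and duration of effect in both arms.

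The size cannot be fixed from the document: about 1-2% if supervoids are slightly larger than usual, and 4-17% if three supervoids at 1.25 to 2 times usual volume fall among 18 diary voids. A reader might infer that the definition manufactures responders. Under these assumptions it does not reach the 50% cut alone; it moves across the cut children who are already near it. Nor should the 4-17% be read as a share of the planned 20-point difference, because that difference is between arms.

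The week-1 reference is a separate and smaller fault. It conflicts with the general outcome rule and lacks a matching entry in the listed forms.

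**What to change.** **AVV.** Report AVV change and the response classes in two versions: all voids, and marked supervoids left out of both the volume sum and the void count. Rest within-arm and responder statements, including duration of effect, on the version without supervoids. The between-arm primary test may keep the all-voids AVV, with the other version as a sensitivity analysis, so the primary endpoint need not be redefined after recruitment has begun.

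**Supervoid outcome.** Replace change from week 1 by a between-arm comparison of week-12 mean supervoid volume, adjusted for pre-treatment baseline AVV. Reconcile Outcomes {12}, the supervoid section and the list of case report forms.

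**Cost.** The data are already planned, since supervoids must be identified for their own outcome. The AVV part adds an analysis and some wording. The supervoid part changes a secondary outcome and its planned test, so it should be documented as an amendment before the research assistant is unblinded. Two downsides remain: up to about 3 of 18 voids leave the 12-week average, and the result depends on supervoids being marked. Unmarked delayed voids at baseline, in children with earlier urotherapy, would pull the change in the supervoid-free version downward, which is a further reason to show both versions.

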#### Secondary outcomes

##### The mean volume of supervoids

This is the median change in the mean volume of three “supervoids” between week 12 and week 1, registered on the 3 days daytime bladder diary. See the “Interventions” section for the definition of supervoids. Same as for the primary outcome, this outcome reflects the change in bladder capacity.

##### Number of urgency incontinence episodes during daytime and night-time

This is the median change of urinary incontinence episodes compared to baseline registered in a 3 days daytime bladder diary and night-time bladder diary (the average of 7 nights).

For parents and participants, this is the most relevant clinical outcome since it significantly affects daily activities mostly.

##### Mean voiding frequency during daytime

This is the median change in diurnal voiding frequency registered in the 3 days daytime bladder diary.

##### Parents reported satisfaction of urinary symptoms

Parents are asked to rate the following question: ‘How would you feel as a parent or guardian if your child’s bladder symptoms were to remain as they are on at this moment?” A score on a Likert-scale from 1 (extremely dissatisfied) to 7 (extremely satisfied) at baseline and after 12 weeks of treatment must be given.

The parent or guardian is the most trustworthy source to obtain a subjective assessment. Therefore, a parent reported instead of patient reported outcome is obtained.

##### Duration of effect

The duration of persistent partial or complete response during the observation period of 6 weeks, expressed in weeks. Same as during the treatment period, one diurnal bladder diary must be completed every week. This tells us more about the maintenance of clinical effect that is either received by active stimulation plus urotherapy or by urotherapy alone and a potential placebo effect.

### Participant timeline {13}

For a participant timeline see Fig. 3.

**Fig. 3 Fig3:**
[figure not shown]
Participant timeline TaPaS trial

For a schedule of enrolment, interventions, and assessment, see Table 1.

### Sample size {14}

For the sample size calculation, an online software package was used:

Sealed Envelope Ltd. 2012. Power calculator for continuous outcome superiority trial. [Online] Available from: https://www.sealedenvelope.com/power/continuous-superiority.

The trial has a parallel superiority design. Based on the previous study by Patidar et al. [8], a mean difference of 20% in the primary outcome (i.e., percentage difference in AVV between baseline and after 12 weeks) between TTNS and sham can be expected, with an estimated standard deviation of 20. A sample size of 24 participants (12 in each treatment arm) is then required to achieve a power of 80% for two-sided testing at a 5% significance level.

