### Statistical methods

#### Statistical methods for primary and secondary outcomes {20a}

Statistical analyses will be performed using SPSS version 25.0. Descriptive statistics of demographic characteristics will be presented by median and interquartile ranges (IQR) for continuous variables and frequencies and percentages for categorical variables. Since the small sample size, non-parametric tests will be chosen. In case a subject withdraws early, a new participant will replace them till the required sample size is reached. An ITT will be performed. If case data are missing, missing data will be imputed via multiple imputation.
° Intra-arm analyses (baseline vs. 12 weeks):Baseline and 12 weeks follow-up absolute values and absolute change and percentage change from baseline values will be presented as medians (IQR). Intra-arm analyses will be assessed using a two-sided Wilcoxon signed rank test.° Inter-arm analyses (sham versus TTNS therapy): differences in absolute and percentage change from baseline between both groups will be reported as medians (IQR) and will be presented with a 95% confidence interval.

Inter-arm analyses will be assessed using a two-sided the Mann-Whitney *U* test

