### Dissemination plans {31a}

In case the superiority of TTNS over sham therapy is proven, phase II of the TaPaS trial will be launched. Since showing the non-inferiority of TTNS compared to PTNS is the ultimate objective of the TaPaS trial, only results of part II will be communicated to a broader public. Trial results of part I will be submitted in the form of an original article for peer review in a not yet determined journal.

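### The sample size inputs give 32 children, not 24; with 24 the power is about 61–69%, not the stated 80%

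*Protocol article*

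**What the plan says.** All inputs stand in one place, section Sample size {14} of the protocol article. The section names an online calculator for a continuous-outcome superiority trial with parallel groups. The effect is "a mean difference of 20% in the primary outcome (i.e., percentage difference in AVV between baseline and after 12 weeks) between TTNS and sham", taken from an earlier sham-controlled trial, "with an estimated standard deviation of 20". The conclusion is: "A sample size of 24 participants (12 in each treatment arm) is then required to achieve a power of 80% for two-sided testing". The stated type I error is 5%.

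Three other sections bear on the point:

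- Trial design {8} fixes 1:1 allocation.
- Statistical methods {20a} says "Since the small sample size, non-parametric tests will be chosen", and names a two-sided Mann-Whitney U test for the comparison between arms. It also says that early withdrawals are replaced until the required number is reached.
- Dissemination plans {31a} ties the next stage to this result: "In case the superiority of TTNS over sham therapy is proven, phase II of the TaPaS trial will be launched".

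**The concern.** The difference equals the SD, so the standardised effect is 1.0. For that effect, a two-sided 5% test with 80% power is well known to need about 16 or 17 per arm. Twelve per arm is visibly too few, and nothing in the section would lower the requirement.

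Part I decides whether part II goes ahead. The Background describes two earlier sham-controlled trials in children, of 20 and 40 participants, with contradictory results, and part I is set up in response. If its real power is well below 80%, a true effect of the assumed size is missed much more often than the protocol says. A reader who trusts the 80% would also give a non-significant result more weight as evidence against the treatment than it can carry.

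**Working it through.** **Inputs** (Sample size {14}, with allocation from Trial design {8}): difference δ = 20 percentage points; SD σ = 20; two-sided α = 0.05, so z = 1.960; power 80%, so z = 0.842; allocation 1:1; no dropout inflation.

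**1. Attempt to reproduce 24.** For two means, by normal approximation:

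n per arm = 2 (z₀.₉₇₅ + z₀.₈₀)² (σ/δ)² = 2 × (1.960 + 0.842)² × (20/20)² = 15.70, rounded up to **16 per arm, 32 in total**.

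The stated 12 per arm (24 in total) is not reproduced; it is 8 children short.

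**2. Power with 12 per arm.**

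- Normal approximation: Φ(δ / (σ√(2/12)) − 1.960) = Φ(2.449 − 1.960) = Φ(0.489) = **68.8%**.
- t test (noncentral t, 22 df): **64.9%**.
- Mann-Whitney U, simulated with normal data, equal SDs and a shift of 1 SD (20,000 runs): **about 61%**.

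**3. Like-for-like comparison by method.**

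| Method | Power at 12 per arm | Chance of missing the effect | Needed for 80% power |
|---|---|---|---|
| Normal approximation | 68.8% | 31% | 16 per arm (32) |
| t test | 64.9% | 35% | 17 per arm (34); 16.71 before rounding |
| Mann-Whitney, normal data | about 61% | 39% | 18 per arm (36); simulated power 78% at 17, 80% at 18 |

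**4. What would make 12 per arm correct?**

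- *One-sided 5% test (or two-sided 10%):* 2 × (1.645 + 0.842)² = 12.37, so 13 per arm and 26 in total. With 12 per arm, normal-approximation power is 78.9%. This comes closest to 24, but it contradicts the protocol's "to achieve a power of 80% for two-sided testing at a 5% significance level".
- *Larger difference:* at SD 20, 80% power with 12 per arm needs 20 × 2.802 × √(2/12) = 22.9 points (normal approximation). By the t test it needs 1.197 × 20 = 23.9 points.
- *Smaller SD:* at a difference of 20, the SD would have to be about 17.5 (normal approximation) or 20/1.197 = 16.7 (t test).
- *Replacement of withdrawals:* this only keeps the number at 24.

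**5. Precision with 24 children.** The half-width of a t-based 95% interval for the mean difference is 2.074 × 20 × √(2/12) = 16.9 points.

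**6. Does the shape of the data matter for the planned test?** The protocol does not say that percentage change in AVV is normally distributed. I simulated the Mann-Whitney test at 12 per arm with a shift of 1 SD under shapes that are my own assumptions. Power was about 61% for normal data, 70% for t with 5 df, 76% for lognormal (sigma 0.5) and 80% for exponential. The 61% is therefore conditional on normality. A t test on the same data had 65–69% power throughout.

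**The case against.** The arithmetic cannot seriously be contested, but four points can be made for the plan.

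- **The 61% depends on normal data.** This stands. For heavy-tailed or skewed changes the Mann-Whitney test can do better than the t test, and for one strongly skewed shape it reaches about 80%. Any restated figure for that test should carry the condition. It does not rescue the protocol, whose number comes from a calculator working with a mean difference and an SD, with no distributional argument. On that basis the answer is 32.
- **The text shows an inconsistency, not which number is wrong.** This also stands. An SD of about 17.5 or a difference of about 22.9 would fit 12 per arm, and the difference is attributed to a study not at hand here. A rounded or misreported input is possible, though nothing in the protocol points to one. The inputs should be checked first.
- **Part I is openly a small trial to obtain the group's own data, and Statistical methods {20a} already plans a 95% confidence interval.** A small trial is legitimate, and the interval is useful. But the stated objective is superiority, and that result gates part II, so the power claim has to be true. How a null result would in fact be read is a matter of judgement, since the protocol does not say.
- **The choice of method changes the size of the shortfall.** True: like for like, 32 goes with 69%, 34 with 65% and 36 with 61%. The smallest of these shortfalls is still 11 points.

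**Conclusion.** The concern holds. On the protocol's own inputs the required total is 32 by the standard formula (34 for a t test, about 36 for the planned Mann-Whitney test with normal data), against the 24 stated. With 24 children, power is about 61–69% depending on method, so the risk of missing an effect of the assumed size is roughly one and a half to two times the 20% implied. 80% power is reached only for a difference of about 23–24 points at SD 20.

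The normal-approximation and t-test figures need nothing beyond the stated difference, SD, two-sided 5% level and 1:1 allocation, plus the usual assumption of normal data with equal SDs. The Mann-Whitney figures rest on that assumption more heavily. That 24 arose from a one-sided calculation is a plausible guess, not something the protocol shows. The power statement is wrong as written and must be corrected.

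**What to change.** 1. Check the difference, SD and sidedness against the original calculator run. If one of them was misreported, correct it in Sample size {14} and give its source.
2. If the inputs stand, replace the power statement, for example: *With 12 children per arm, a 20-point difference and an SD of 20, power is about 65% (two-sided 5% t test), or about 61% for the planned Mann-Whitney test if percentage changes are normally distributed; 80% power is reached for a difference of about 24 points.*
3. Add a sentence to Statistical methods {20a} or Dissemination plans {31a} that a non-significant part I will be read through the 95% confidence interval already planned, and not as absence of effect.

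Steps 1 to 3 cost wording only; the published power becomes less favourable. If the sponsor prefers to keep the 80% claim, the matching total is 32 (normal formula), 34 (t test) or 36 (Mann-Whitney with normal data), which means 8 to 12 more children. Trial status describes recruitment as still under way and delayed by the pandemic, so that decision is the sponsor's.
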